### Data acquisition

#### Blood parameter

To assess peripheral inflammation and fasting metabolism, blood samples are collected at the beginning of each session. Glucose, insulin, triglycerides, HDL, LDL, HbA1c, and differential blood counts are analyzed by the Central Laboratory of the University Hospital Bonn. EDTA plasma (untreated and treated with aprotinin (500 KIU/ml)) will be immediately processed after the blood draw (centrifugation settings: 4 °C, 10 min, 2000 g) and then stored in aliquots at -80 °C. These plasma aliquots will be used to analyze additional hormones with ELISA kits, and to assess plasma levels of pro- and anti-inflammatory cytokines and other biomarkers of inflammation using highly sensitive immunoassays (e.g., NULISA).

In addition to the standard differential blood count, we will evaluate circulating immune cells by analyzing peripheral blood mononuclear cells (PBMC) that are isolated from fresh human peripheral blood by density gradient separation using Ficoll™ Paque Plus (cytiva, Sweden). In brief, whole blood is collected into EDTA-containing tubes (SARSTEDT, Germany). Blood is diluted 1:1 with Dulbecco’s Phosphate Buffered Saline (DPBS; Thermo Fisher Scientific, USA) and carefully layered onto 15 mL of Ficoll™ Paque Plus. Samples are centrifuged (700 g, 20 min, room temperature) and the PBMC layer is collected and washed using DPBS. Residual erythrocytes are removed by incubating the sample 3 min in red blood cell lysis buffer (BioLegend, USA). Afterwards, the cells are washed again using DPBS. Cell counts and viability are determined with 0.4% Trypan Blue Stain (Thermo Fisher Scientific, USA) using the automated TC20™ Cell Counter (Bio-Rad, USA), ensuring high cell viability for subsequent experiments. To quantify circulating immune cells from PBMCs, we will assess immune cells in three different panels (see Table 1, for an overview of all antibodies and gating strategies, see SI). Briefly, we incubate the cells for 10 min at room temperature with human FcR Blocking Reagent (Miltenyi, Netherlands) to block unspecific binding sites. Afterwards, cells are incubated with the corresponding antibodies (4 °C, 30 min, light protected). Samples are washed twice with staining buffer solution (1 x PBS supplemented with 2 mM EDTA and 0.5% BSA) and finally the cells of each panel are resuspended in 200 µL of staining buffer solution. Stained samples are acquired on a flow cytometer (Attune NxT, Thermo Fisher). Data will be analyzed using FlowJo (BD Biosciences) and R [73, 74].

**Table 1 Tab1:** circulating cells investigated using flow cytometry

T-cell panel 1	T-cell panel 2	Monocytes and dendritic cells
CD4 + Tconv	CD4 + T-helper cells	Dendritic cells
Naïve	Th1	cDC1
Central memory	Th1.17	cDC2
Effector memory	Th2	pDC
TEMRA	Th17	
CD8 + T-cells		Monocytes
Naïve		Classical
Central memory		Non-classical
Effector memory		Intermediate
TEMRA		
CD4 + Treg		
Activated		
Resting		

*Tconv* conventional T-cells, *TEMRA* terminal effector memory re-expressing CD45RA, *Treg* regulatory T cells, *cDC* conventional dendritic cells, *pDC* plasmacytoid dendritic cells

#### Diffusion weighted imaging acquisition and preprocessing

To assess central inflammatory responses to tVNS, we acquire one planar AP diffusion weighted imaging (DWI) sequence (voxel dimensions: 2 × 2 × 2 mm, TE = 95 ms, TR = 10,000 ms, transverse orientation, flip angle = 90°, 26 directions, b-values ranging from 0 to 1400 s/mm^2^) and two non-diffusion images (b-value = 0, one in AP and one in PA direction, respectively) per participant and MRI session using a 3 T Siemens scanner (Magnetom Trio) with a 32-channel head coil. Data will be preprocessed using the FSL [47] command *fslmerge*, *eddy correct* and *topup* [3], and the diffusion basis spectrum imaging (DBSI) Toolbox (MATLAB code) kindly provided by [name] [95]. Thereby, we will calculate proxies for tissue edema (isotropic diffusion (*f*(D), D = 0.3–3.0 µm^2^/ms), cellularity (isotropic diffusion (*f*(D), D ≤ 0.3 µm^2^/ms), and dendrite/axonal density (anisotropic diffusion) as readouts of central inflammation.

#### fMRI data acquisition and preprocessing

fMRI images are collected at rest (10 min) and during the EAT. Task fMRI will be used to measure brain responses related to reward, effort, and invigoration. All fMRI data will be used to investigate functional connectivity. We acquire T2*-weighted echo-planar imaging (EPI) sequences (40 ascending axial slices to cover the whole brain, TR = 2.66s, TE = 30ms, flip angle = 77°, matrix size = 64 × 64, field of view = 192 × 192 mm², and voxel size = 3 × 3 × 3 mm³). To control for inhomogeneity of the magnetic field, we acquire a field map, Siemens gradient echo field map sequence: short TE = 4.92ms, long TE = 7.38ms. For anatomical co-registration, a structural T1w image is collected at the beginning of each session (208 sagittal slices, flip angle = 9°, matrix size = 320 × 320 and voxel size = 0.8 × 0.8 × 0.8 mm³). Imaging data will be preprocessed using fMRIprep [24]. Smoothing ([8 8 8] mm) and first-level statistics will be implemented in SPM, version 12 (Wellcome Department of Imaging Neuroscience, University College London, London, UK [39]). Regions of interest will be defined by an extended version of the Harvard-Oxford brain atlas [21, 72, 89]. The following regressors will be included in the default first-level models: anticipatory phase (onset when reward cues are shown, duration = 0s), the work phase (duration = 15s), and feedback presentation (duration = 0s). The cue regressor is modeled separately for food and money trials and both include a parametric modulation by reward magnitude (low, high). The regressor for the work phase includes a parametric modulator for difficulty (low, high) and the feedback regressor parametric modulations for reward magnitude and difficulty. Moreover, we will include regressors capturing the exerted effort at that time: force/TR and the change in force from timepoint to timepoint: delta(force)/TR. To test the effects of tVNS in pre-specified regions of interest, we will extract average contrast estimates from the individual images for each session and analyze them using linear mixed-effects models. In addition, we will explore voxel-wise whole-brain effects using second-level full factorial models in SPM. The main contrasts of interest are reward magnitude effect for cue anticipation across food and money trials and delta(force)/TR to capture invigoration.

#### Self-reported questionnaires

Participants are asked to fill out self-reported questionnaires to characterize the sample at baseline and to track additional symptoms over the course of the study. To assess eating behavior at baseline, we use the Eating Disorder Examination Questionnaire [27], the Salzburg Emotional Eating Scales [63], the Salzburg Stress Eating Scales [64], the Three-Factor Eating Questionnaire [88], and the Food Cravings Questionnaire-Trait-reduced [62]. In addition, we collect questionnaires on substance use (Alcohol Use Disorder Identification Test [81], Cannabis Use Disorders Identification Test [5], Fagerstrom Test for Nicotine Dependence [25]). Moreover, participants report somatic symptoms using the Patient Health Questionnaire-15 [53], anxiety using the Liebowitz Social Anxiety Scale [60] and State-Trait Anxiety Inventory-Trait [59], and trait motivation using Behavioral Inhibition System/Behavioral Approach System scales [15].

Over the course of the study (i.e., at baseline and after 14 days of each stimulation), we assess symptoms of depression (Beck Depression Inventory II, BDI-II [45]), anhedonia (Snaith-Hamilton Pleasure Scale in German, SHAPS-D [37]), and apathy (Apathy Motivation Index, AMI [4]). In addition, we assess physical activity using the International Physical Activity Questionnaire [19] and interoception using the Multidimensional Assessment of Interoceptive Awareness (v2) [61] and the Visceral Sensitivity Index [57] questionnaire. We assess eating behavior using a food frequency questionnaire (DEGS, [44], the Yale Food Addiction Scale [41], and the Power of Food Scale [12]. We also systematically record potential tVNS side effects, participants’ expectations regarding tVNS, and blinding.

#### Data management and quality assurance

Data on behavioral tasks and on self-reported questionnaires are collected using electronic data capture systems. All data are then securely transferred to institutional servers. All personal data is password-protected and all data are acquired and stored in pseudonymized form until data collection has been completed. After study completion, all data will be anonymized. To ensure consistency and reliability across sessions, data acquisition follows standardized protocols including instructions on tVNS usage and calibration. Blood sampling and the MRI acquisition is performed by trained personnel with medical or psychological background. To enhance transparency, reproducibility, and adherence to open science principles, open-access analysis scripts of the EAT are available via GitHub (https://github.com/neuromadlab/Tasks/tree/master/Effort_Allocation_Task/Analyses/general). Using customized MATLAB scripts, the study team monitors adherence to stimulation protocols, completion of EMA, questionnaires and assessment of primary outcomes. As the study poses minimal risks and involves a short intervention period, safety is monitored by the study investigators in accordance with ethical oversight requirements. No further outcome data will be collected for participants who have discontinued. No formal auditing is planned. Any substantial changes to the study protocol will be communicated to the ethics committee and trial registries as appropriate.

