### Intervention: transcutaneous Vagus Nerve Stimulation (tVNS)

All participants are instructed to stimulate the right cymba concha, a region that is innervated by the auricular branch of the vagus nerve [36]. We use tVNS R (tVNS technology, Erlangen, Germany) that enables the adjustment of stimulation parameters and logging of use outside the lab. For the high-intensity stimulation, the intensity is set to an individually calibrated amplitude corresponding to a mild pricking sensation (using a staircase procedure). We use the conventional stimulation protocol (30 s ON, 30 s OFF, 25 Hz frequency, 250 µs pulse width) [34, 69]. If participants report a painful stimulation after the initial calibration, we will lower the stimulation intensity in steps of 0.1 mA, until the stimulation corresponds to mild pricking again. For the low-intensity stimulation, the amplitude is set to the minimum of 0.1 mA (1 s ON, 30 s OFF, 1 Hz frequency, 250 µs pulse width). This amplitude is too low to activate vagal afferent fibers [29]. Participants will be unblinded and excluded if continued tVNS may pose a health risk to them (e.g., due to changes in criteria that preclude safe use).

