#### Statistical analysis population

The modified intention-to-treat (mITT) analysis set includes all participants who have been randomized and have completed outcome measures for the baseline (T0) and at least one post-intervention session (T1, either after high-intensity stimulation or after low-intensity stimulation) without major protocol violations. Since mixed-effects models allow missing data, we will conduct all analyses using mixed-effects models on the mITT analysis set. All participants who were randomized but not part of the mITT analysis set will be described. However, since the aim is to investigate the effects of high-intensity tVNS vs. low-intensity tVNS, it is crucial to have completed outcome measures for the baseline and at least one post-intervention session (high-intensity or low-intensity stimulation). We will impute missing values of covariate predictors to maximise the sample size for controlled analyses based on correlated covariates (e.g., body fat values based on BMI, sex, and age or single questionnaire scores).

Major protocol violations include:Changes in participant’s criteria that preclude safe use of tVNS.Insufficient (i.e., 0 minutes logged by the tVNS device) at-home stimulation during the intervention phases

Completion of the study is independent of interim analyses, and the study will continue until the planned sample size is reached. Interim analyses will use the mITT population but include only participants who have completed primary endpoint data at the time of the interim analysis. We record treatment expectations and blinding and will assess the extent to which the results depend on the treatment expectations.

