#### Secondary and other prespecified endpoints

Secondary endpoints are tVNS-induced changes in mood (PANAS), the correlation of tVNS-induced changes in peripheral and central inflammation with tVNS-induced changes in motivation and mood, and whether inflammation is associated with motivational indices or mood indices (orthogonal to the effects of tVNS). Moreover, we will evaluate the broader impact of tVNS across behavioral and mood domains as secondary endpoints (wanting and exertion ratings, utility slopes, mood and motivation in daily life, anhedonia (SHAPS-D), depressive symptoms (BDI-II), and apathy (AMI)). Secondary endpoints will be analyzed using LMEs or robust regression models, as appropriate. For LMEs the same covariates and predictors as described in the section primary endpoints will be used. Secondary outcomes are assessed at baseline and after each stimulation phase. For some secondary outcomes, there is a second baseline measurement before the second stimulation phase. In these cases, we will adjust the model accordingly. Stimulation-induced changes in secondary outcomes will again be compared between high- and low-intensity stimulation.

Other prespecified endpoints are tVNS-induced changes in metabolic blood parameters (triglyceride-glucose-index, HOMA-Index, triglycerides, HDL, LDL, HbA1c, adiponectin, leptin, (acyl-)ghrelin, and GLP-1), body measures (BMI, waist-to-hip ratio, resting heart rate, blood pressure, and percentage of body fat), physical activity, and in eating behavior including decision weights in the food choice task. In addition, we investigate tVNS-induced changes in state ratings in daily life collected via EMA and tVNS-induced changes in self-reported interoception. Stimulation-induced changes in other prespecified outcomes will again be compared between high- and low-intensity stimulation. We systematically assess side effects and will investigate potential predictors of tVNS efficacy.

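### Outcome collection ends at discontinuation with no exemption for side effects, so a participant who leaves mid-phase has no described side-effect report for that phase

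*Protocol article*

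**What the plan says.** Data management and quality assurance: "No further outcome data will be collected for participants who have discontinued". The sentence before it says that the investigators monitor safety.

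Experimental procedure: side effects are asked about at the start of the second session, and Session 4 is run in the same way. The adapted session after washout has no described side-effect question.

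Self-reported questionnaires: side effects are recorded systematically. The sentence stands in a paragraph whose stated times are baseline and after 14 days of each stimulation. The daily items listed under Ecological momentary assessment include painkiller use but nothing on side effects.

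Intervention: "Participants will be unblinded and excluded if continued tVNS may pose a health risk to them".

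Statistical analysis population: the mITT set requires baseline and "at least one post-intervention session (T1, either after high-intensity stimulation or after low-intensity stimulation) without major protocol violations". One listed violation is a change in the participant's "criteria that preclude safe use of tVNS". The article adds that "we will conduct all analyses using mixed-effects models on the mITT analysis set" and that "All participants who were randomized but not part of the mITT analysis set will be described".

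Secondary and other prespecified endpoints: "We systematically assess side effects and will investigate potential predictors of tVNS efficacy". No population, denominator or model is given for side effects.

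Participants: dropouts are replaced until 60 have completed all sessions.

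**The concern.** This point is about the tolerability result, not the efficacy contrast. The Background says that side effects will be recorded and monitored during the intervention, and the Discussion counts safe home use as an advantage of the technique. A credible tolerability result needs reports from the people who stopped as well as from those who carried on.

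Side effects appear among the prespecified endpoints, so a plain reading of the collection rule covers them. Followed as written, the rule shuts off reports from participants who leave between the scheduled questions, and those who leave because of a side effect are among them. An analysis plan cannot recover answers that were never collected.

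The loss may also be unequal between conditions. Low intensity is fixed at 0.1 mA and participants are told it is below the sensation threshold, while high intensity is calibrated to mild pricking. If tolerability stops occur mainly under high intensity, the difference in side effects between conditions would shrink. A participant who completes low intensity first and leaves during high intensity would have a described report for low intensity only.

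**Working it through.** **Step 1: is there a figure to reproduce?** No. The article gives no side-effect rate and no expected number of stops. Its one design calculation (N = 60, d_z about 0.40, power 0.86) does reproduce, at 0.862 for a two-sided paired t-test with alpha 0.05, but this point does not depend on it.

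**Step 2: follow each kind of participant through the stated rules.**

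| Participant | Side-effect question reached? | In the mITT set? |
|---|---|---|
| Stops stimulating but attends the session | Yes | Yes, unless the device logged 0 minutes |
| Leaves in phase 1, before Session 2 | No | No (no post-intervention session) |
| Leaves in phase 2, not for a safe-use reason | Session 2 only; none for phase 2 | Yes |
| tVNS becomes unsafe in phase 1 | No | No |
| tVNS becomes unsafe in phase 2 | Session 2 only; none for phase 2 | No, despite having baseline and Session 2 data |

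The collection gap is in rows 2 to 5. Removal by the safe-use violation applies only to the last two rows.

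**Step 3: how much could it matter?** The inputs here are assumptions, not figures from the article. Suppose 60 participants give session reports, x of them report a side effect, and k further participants stopped because of a side effect that went unreported.

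Rate from session reports = x/60. Rate among all treated = (x + k)/(60 + k).

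| k | x = 6 (6/60 = 10.0%) | x = 12 (12/60 = 20.0%) | Stops among all treated |
|---|---|---|---|
| 0 | 6/60 = 10.0% | 12/60 = 20.0% | 0/60 = 0% |
| 1 | 7/61 = 11.5% | 13/61 = 21.3% | 1/61 = 1.6% |
| 3 | 9/63 = 14.3% | 15/63 = 23.8% | 3/63 = 4.8% |
| 6 | 12/66 = 18.2% | 18/66 = 27.3% | 6/66 = 9.1% |

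For one to six such stops, the understatement is 1.5 to 8.2 percentage points when the session-report rate is 10%, and 1.3 to 7.3 points when it is 20%. With k = 0 nothing changes. A summary confined to the 60 would show no stops, whatever k is.

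**Limits of the illustration.** It pools the two conditions. It assumes that every stop had a side effect and that none was recorded another way. It also treats the 60 as the whole reporting group, although the mITT set admits non-completers who have one post-intervention session.

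**The case against.** A reader might infer that the side-effect rate will be reported on the mITT set, so that intolerant participants are removed by rule from numerator and denominator. The article does not say this, and the objection is right on several counts:

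- The mITT rule is written for mixed-effects analyses. No denominator is given for side effects, and randomised participants outside the set are to be described.
- A statistical analysis plan is said to be on OSF and is not shown. It may define a safety population, so the absence of one from the article is not a fault in itself.
- A change in safe-use criteria can be a new contraindication unrelated to tVNS, so not every such exclusion bears on tolerability.
- Participants who withdraw in phase 2 for ordinary intolerance, with baseline and Session 2 data, stay in the mITT set.
- Some events may be captured in other ways. The investigators monitor safety, the Intervention section provides for participants who report painful stimulation after calibration, and a team that excludes someone for a health risk knows of that risk. The collection rule looks forward: it does not delete what was already recorded, nor does it say that adverse-event recording stops.

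All of this stands, and it removes any claim that the reported rate will be biased. It does not remove the collection gap. The rule is stated, it makes no exception for side effects, and the described questions are tied to sessions that a participant who has left does not attend. A promise to describe these participants cannot supply answers that nobody asked for.

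**Conclusion.** The concern holds as a problem of data collection, with a conditional effect on reporting. As written, participants who leave mid-phase have no described side-effect report for that phase, and those for whom tVNS becomes unsafe also drop out of the only named analysis set. If side effects are summarised only from session reports or on the mITT set, the rate may be too low, and possibly more so under high intensity.

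The size cannot be determined from the article. The figures above rest on assumed side-effect and stopping rates, and the effect is zero if nobody stops for this reason. The article does not support the stronger conclusion that understatement is certain or planned. The correction is still worth making, because tolerability at home is something the trial intends to speak to and the change costs little.

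**What to change.** 1. Limit the sentence in Data management and quality assurance to outcomes other than side effects.
2. State that the existing side-effect questions are completed by phone or online at any discontinuation.
3. State that side effects and reasons for stopping are reported, by the condition in use, for everyone who received any stimulation, regardless of the mITT exclusions. If the analysis plan on OSF already says this, a cross-reference is enough.

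The cost is one amended sentence, one added reporting statement and a short contact per discontinued participant. The reported rate may look less favourable. At submission 27 of the planned 60 had completed and recruitment was continuing, so the change can still apply to the remaining participants (60 − 27 = 33 completions outstanding).

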#### Participant retention and follow-up

To improve compliance with the study protocol, participants receive a completion bonus as monetary compensation. In addition, participants also receive daily reminders to complete EMA and perform the tVNS stimulation. Participants are also informed that the tVNS devices record their use.

### Statistical analyses

#### Baseline characteristics and group comparisons

Descriptive statistics will be reported for age, sex, BMI, waist-to-hip ratio, use pattern of tVNS (e.g., frequency, duration; split by high and low-intensity stimulation), and depressive symptoms (BDI-II). Statistical analyses will be reported using summary tables and figures. Continuous variables will be summarized with means and standard deviations. Categorical variables will be summarized by counts and by percentage of participants.

